- What is the effect of Enhanced Adherence Counselling on rates of being alive, in care, and virally suppressed within 3 and 12 months of intervention eligibility?

*Objective 5: Among HIV-infected patients in antiretroviral therapy programs who miss a scheduled appointment by 5 days,* ***evaluate the impact of Early Patient Tracing on retention in care****.*

Research questions:

- What is the effect of Early Patient Tracing on rates of returning to care by 3 and 12 months of tracing?
- What is the effect of Early Patient Tracing on rates of remaining in care by 12 months of tracing?

*Objective 6: For each clinic included in the study,* ***evaluate the overall impact of the Adherence Guidelines on patient outcomes****.*

Research questions:

- What is the effect of the package of interventions on patient retention in care overall?
- What is the proportion of population in need expected to benefit from the package of interventions?

*Objective 7:* ***Estimate the incremental and total cost of each of the interventions*** *listed above compared to standard of care.*

Research questions:

- What is the average cost per patient reached with the intervention?
- What is the average cost per successful outcome achieved?

*Objective 8:* ***Describe the current status of the cascade of care and adherence to treatment for tuberculosis, hypertension, and diabete****s, for the purpose of tailoring the minimum package of interventions to these conditions in the national rollout.*

Research questions:

- What is the prevalence of previously and newly diagnosed TB, hypertension, and diabetes among the population of patients presenting for care at primary health clinics, stratified by age, sex, and HIV status where possible?
- What proportion of diagnosed cases of these conditions are initiated on guideline-compliant treatment?
- What proportion of cases have satisfactory outcomes, based on current guidelines 12 months after diagnosis?
- For each condition, what proportion of patients are lost to care or discontinue treatment during the first 12 months after diagnosis?

Note that the impacts being assessed under Objectives 1-6 are the impacts of the interventions as implemented in the early phase of the national rollout of the guidelines. As is the case with program evaluations in general, results will reflect both intervention efficacy and implementation quality, which may in turn reflect the early learning stage of national policy implementation.

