## **b. Inclusion and Exclusion Criteria**

For Objectives 1-5 and Objective 8, we will enroll a specific cohort of patients. These will be numbered in accordance with the objective number for Objectives 1-5; for Objective 8, the cohort will be called the “TBHD cohort”, in reference to tuberculosis, hypertension, and diabetes. This TBHD cohort will be made up of patients who have been screened for TBHD (50%) and patients who are newly diagnosed with TB, hypertension or diabetes (50%). For all cohorts, inclusion and exclusion criteria are as shown below. For Objectives 1-5, these criteria follow the December 2014 national guidelines for HIV care and ART[10] and November 2015 National Adherence Guidelines for Chronic Disease (HIV, TB and NCDs) [11].

*Cohorts 1-5 and TBHD cohort inclusion criteria*

- ≥ 18 years old
- Meet the inclusion criteria for one or more of Cohorts 1-8

*Cohorts 1-5 and TBHD cohort exclusion criteria*

- Not resident in the facility’s catchment area
- Recorded intention to transfer care to a different facility within 12 months
- Pregnant and eligible for PMTCT

*Objective 1/Cohort 1 inclusion criteria (Patients newly eligible for ART—fast track treatment initiation)*

- Determined to be eligible to start ART under prevailing national guidelines (CD4 count < 500, WHO Stage 3 or 4 condition, TB, cryptococcal meningitis)

*Objectives 2 and 3/Cohorts 2 and 3 inclusion criteria (Patients stable on ART—adherence clubs or decentralized medication delivery)*

- On same ART treatment regimen for at least 12 months
- Most recent viral load taken in past 6 months
- Two consecutive viral loads undetectable (<400 copies/ml^3^)

*Objective 4/Cohort 4 inclusion criteria (Patients on ART with poor adherence—enhanced adherence counseling)*

- On first line ART for at least 6 months
- Poor adherence as indicated by an elevated viral load (>400 copies/ml^3^)

*Objective 5/Cohort 5 inclusion criteria (Patients lost from ART programs—early patient tracing)*

- Initiated ART
- Fail to return for a scheduled appointment within 5 to 90 days from their appointment date

*Objective 8/TBHD cohort inclusion criteria (Tuberculosis, hypertension, and diabetes patients)*

- Screened for or diagnosed with for TB or hypertension within the last month, or diabetes within last 6 months

*Objective 8/TBHD cohort exclusion criteria (Tuberculosis, hypertension, and diabetes patients)*

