- Patients with existing TB, hypertension (diagnosed more than 1 month ago) or diabetes (diagnosed more than 6 months ago)

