## **c. Duration of Follow Up**

Study enrollment will begin on the date of determination of eligibility for an intervention (Cohorts 1-5) during the enrolment period. Enrolment for cohort 8 will begin if date of eligibility (screening or diagnosis date) was in the last month for TB and Hypertension patients and within the last 6 months for Diabetes patients.

Passive follow up through medical record review will continue for a minimum of 14 months after the date of enrollment (two additional months beyond twelve months to allow one year outcomes to occur). This will allow all subjects sufficient follow up time to complete each of the primary outcomes designated. Patients enrolled early in the study will have up to 20 months of passive follow-up, assuming a six-month enrollment period. Medical records will be checked for each patient after each clinic visit.

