| Overall impact (Objective 6) | Proportion of population in need at each clinic who achieve the short term primary outcomes defined above. | Proportion of population in need at each clinic who achieve the long term primary outcomes defined above. |
| Cost  (Objective 7) | Average cost per patient receiving an adherence intervention | Average cost per primary outcome achieved; average cost per 1000 patients receiving the observed mix of interventions |
| TB, hypertension, and diabetes (Objective 8) | For each condition, proportion of patients eligible for treatment who have 80% visit compliance in the first three months after diagnosis (S) and who achieve disease control at the six-month visit after diagnosis (L) as indicated in “Primary Care 101,” the NDOH’s guide for primary health clinic services[15]. The six-month visit will be represented by the visit closest to six months within the window of 5-8 months after diagnosis. The disease control indicators to be measured, with page references for Primary Care 101, are:  TB: cured or treatment completed indicated as the patient’s status at 6 months (page 57)  Hypertension: blood pressure controlled at 6-month visit, with control defined as < 140/90 (or 120/70–140/80 if diabetes, or <130/80 if CVD, heart failure or kidney disease) (page 74)  Diabetes: random glucose < 8 or HbA1c ≤ 7% at 6 month visit (page 71) | Among patients screened, prevalence of pre-diabetes elevated blood sugar (defined by Primary Care 101 as random glucose between 7.8 and 11) and pre-hypertension elevated blood pressure that require monitoring  Proportion of patients diagnosed with pre-diabetes or pre-hypertension who a) progress to diabetes and hypertension; or b) remain in care and receive appropriate monitoring for their condition over 12 months  Prevalence of diabetes, hypertension and TB among patients screened  Proportion of diagnosed patients initiated on appropriate treatment  Proportion of patients on treatment retained in care at 12 months. Loss to follow up will be defined as being 30 days late for a scheduled appointment.  Demographic and clinical characteristics of patients who do and do not achieve primary outcomes. |

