| Objective 7—Cost | 0 patients | No additional subjects will be enrolled for the cost estimates, which will rely on data from Cohorts 1-5. |
| Objective 8—TB, hypertension, and diabetes | 4800 patients | Because Objective 8 is descriptive in nature, no specific sample size will be targeted. We will instead include up to the first 100 patients per site who are eligible for screening and 100 patients who are recently diagnosed and treated for TB, hypertension and/or diabetes, for a total of 4800. (We note that some patients eligible for the TBHD cohort will also be eligible for Cohorts 1-5, due to co-morbidities with HIV. These patients will be co-enrolled in both cohorts.) |

Total enrollment will thus be 2,880 in cohorts 1-5 and 4,800 in the TBHD cohort, for a total sample size of 6,680.

Due to the size criterion for study site selection, with all clinics included in the evaluation having at least 1,000 current ART patients, we anticipate being able to enroll the target sample sizes for all cohorts during a 6-month enrollment period. Enrollment for Cohorts 4 and 5 and 8 may take longer than this depending on baseline rates of viral suppression and visit compliance at the selected clinics and number of newly screened and diagnosed TBHD patients.

We will monitor the data for Cohorts 1-5 closely and amend the protocol to increase the sample size for these cohorts if needed to ensure adequate analytic power.

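### The TBHD exclusion is worded for the patient, not the index condition, so read literally it drops newly screened or diagnosed patients who already have another of the three conditions

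*Protocol*

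**What the plan says.** Section 8b (Inclusion and Exclusion Criteria) sets up one TBHD cohort for Objective 8, half of it screened patients and half newly diagnosed patients. One inclusion line covers all three conditions: "Screened for or diagnosed with for TB or hypertension within the last month, or diabetes within last 6 months". One exclusion line also covers all three: "Patients with existing TB, hypertension (diagnosed more than 1 month ago) or diabetes (diagnosed more than 6 months ago".

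Section 9c (Duration of Follow Up) repeats the windows. Enrolment depends on an eligibility date that "was in the last month for TB and Hypertension patients and within the last 6 months for Diabetes patients". It adds no condition-specific exclusion.

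The first research question under Objective 8 (section 3c) is: "What is the prevalence of previously and newly diagnosed TB, hypertension, and diabetes among the population of patients presenting for care at primary health clinics". Table 3 lists disease control for each condition as a primary outcome and the prevalence of the three conditions among screened patients as a secondary one. Its hypertension outcome reads "blood pressure controlled at 6-month visit, with control defined as < 140/90 (or 120/70–140/80 if diabetes", followed by a further limit for some other conditions. Table 4 plans up to the first 100 patients per site eligible for screening, plus "100 patients who are recently diagnosed and treated for TB, hypertension and/or diabetes".

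**The concern.** The exclusion acts on the patient. It lists three conditions joined by 'or' and does not refer back to the condition for which the patient was screened or diagnosed. A patient can therefore meet the inclusion line through one condition and be removed because of another.

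Objective 8 is meant to describe the care cascade for each condition, so that adherence support can later be tailored to these patients. People already attending for one chronic condition who are then screened for or diagnosed with a second belong to the population presenting for care. If they are never enrolled, the descriptive estimates apply to a narrower group than the objective names.

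**Working it through.** **1. The plan's own figure.** Table 4 gives 4,800 for this cohort. With 24 sites (section 8a) and 100 screened plus 100 diagnosed per site (Table 4), 24 × (100 + 100) = 4,800, which reproduces. The diagnosed half is 24 × 100 = 2,400. The point concerns who fills these places, not how many there are.

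**2. The two readings applied to example patients.**

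| Patient | Inclusion met through | Literal exclusion | Exclusion per condition |
| --- | --- | --- | --- |
| Diabetes diagnosed this month, hypertension known for two months | Diabetes | Out | In for diabetes, out for hypertension |
| TB diagnosed this month, diabetes known for more than 6 months | TB | Out | In for TB, out for diabetes |
| Screened for TB this month, hypertension known for more than 1 month | TB screening | Out | In for TB, out for hypertension |
| Hypertension diagnosed this month, diabetes known for more than 6 months | Hypertension | Out | In for hypertension, out for diabetes |
| Hypertension diagnosed this month, diabetes diagnosed within 6 months | Either | In | In for both |

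The readings differ whenever one condition is new and another is established. They agree when every condition is recent.

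**3. Against the objective.** The research question covers previously as well as newly diagnosed disease among patients presenting for care. On the literal reading, nobody in the cohort has a diagnosis older than the window. Prevalence among patients screened then has a denominator cleared of established disease, and each cascade is conditional on having no other established condition.

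**4. Whether analysis could repair it.** Section 9d enrols consecutively until the targets are met, so an excluded patient is replaced and no data are collected on that patient. Section 10f stratifies by clinic, province, sex, age group and HIV status, not by other established conditions. Neither weighting nor stratification can restore the missing group.

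**5. Size, on assumptions only.** Let *s* be the share of otherwise eligible patients with another established condition, and *g* the difference in the outcome proportion between kept and excluded patients. The proportion in all patients is (1 − *s*) × kept + *s* × excluded, so the estimate from kept patients alone is off by *s* × *g*. The protocol gives neither value. Assumed values give:

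- *s* = 5%: 0.05 × 2,400 = 120 of every 2,400 diagnosed candidates excluded. Shift 0.05 × 5 = 0.25 points to 0.05 × 20 = 1 point.
- *s* = 20%: 480 excluded. Shift 0.20 × 5 = 1 point to 0.20 × 20 = 4 points.
- *s* = 40%: 960 excluded. Shift 0.40 × 5 = 2 points to 0.40 × 20 = 8 points.

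If *g* is zero there is no shift. The range runs from negligible to material, and nothing in the protocol narrows it.

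**The case against.** The best defence is that the line was meant condition by condition. Its windows (hypertension over 1 month, diabetes over 6 months) are the exact complement of the inclusion windows, and the natural purpose of such a line is to keep prevalent cases of a condition out of the newly diagnosed group for that condition. This is plausible, and it rules out calling the patient-level rule a deliberate choice. It does not supply the missing words, and staff selecting from records at 24 clinics could apply either reading.

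A reader might infer that Tables 3 and 4 contradict the exclusion, because one has a blood-pressure limit for patients with diabetes and the other says 'and/or'. The documents do not support that. A patient with new hypertension and diabetes diagnosed within 6 months is eligible even on the literal reading, so both texts have patients to apply to. The limit also stands in a control definition that the protocol takes from a clinical guide, so it is weak evidence about the case mix expected.

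It is also fair that Objective 8 is descriptive, that the randomised comparisons of Objectives 1 to 5 are untouched, and that HIV comorbidity is expressly kept through co-enrolment. Estimates from the narrower group could still be valid for that group. All of this stands and limits the weight of the point.

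**Conclusion.** The point holds as a defect of wording with a real consequence. Followed as written, the exclusion yields a population narrower than the one Objective 8 asks about, for both the screened and the diagnosed halves. That conclusion rests on the text alone and needs no assumed figure.

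A stronger reading is tempting: that every condition-specific estimate is biased by several points. For example, assuming that 30–60% of new diabetes patients have known hypertension and that retention differs by 10–15 points gives 0.30 × 10 = 3 to 0.60 × 15 = 9 points. The documents support neither input, give nothing comparable for TB or for new hypertension with established diabetes, and do not show that outcomes differ at all. What is established is a loss of coverage; bias is possible but of unknown size. Nor does the rule remove all comorbidity, since patients whose conditions are all recent remain eligible.

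The matter deserves correction before enrolment, because it cannot be corrected afterwards.

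**What to change.** Reword the TBHD exclusion so that an established condition excludes the patient only from that condition's cascade, and the patient stays eligible for any other of the three newly screened or diagnosed within its window. Record established TB, hypertension and diabetes at enrolment and add them to the strata in section 10f, so that results can be shown with and without these patients. If the patient-level rule is intended, say so, give the reason, and restate the Objective 8 population to match.

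The cost is one reworded sentence, one extra recorded variable and a more mixed cohort. The target stays at 24 × 200 = 4,800. Wider eligibility should make the places easier to fill, which helps because section 10b warns that enrolment for this cohort may take longer than six months.

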# DATA SOURCES AND MANAGEMENT

## **a. Data Sources**

The NDOH and its partners will implement the interventions listed above as the initial component of a new national policy. This protocol is solely for an evaluation of the impact of the interventions. The study team will have no involvement in providing services nor any interaction with patients. The evaluation will instead rely solely on routinely collected facility-and patient-level records that can be accessed without individual patient consent. Based on our experience in previous studies, we anticipate that each study clinic will have slightly different existing data collection procedures in place, and different provinces may use different versions of standard forms. Study procedures will therefore be adapted on a site-by-site basis before individual patient data collection begins. The National Department of Health will be asked to assure and facilitate access to Tier.Net, DHIS, patient registers and records, and other routinely collected sources of data from the evaluation clinics.

For Objectives 1-5, routine data sources will include Tier.Net data, the National Health Laboratory Service (NHLS) data which contains all laboratory tests done in public-sector clinics, data sets created by entering clinic registers, adherence plans, and patient clinic files into a database. We note that some strengthening of existing data collection procedures will be required at the facilities where the evaluation will take place in order to ensure complete entries into existing clinic registers or patient files, complete and accurate entry of source data onto electronic files, and the use of a consistent clinic-level patient identifier to link patients between data sources (e.g. a register containing a row for each visit and a patient file containing documents pertaining to that patient will each contribute to the evaluation record for that patient). Prior to the start of data collection, we will work with each study clinic to ensure that the registers, stationery and records mandated by the guidelines and the National Health Act are being completed correctly and fully, including new documentation called for by the Adherence Guidelines, such as the individual patient Adherence Plan (AGL SOP Booklet, Annexure 1, p. 66).

For Objective 6, to estimate the overall impact of the package of interventions at each study clinic, we will collect aggregate, clinic-level data on numbers of patients presenting in the most recent 12-month period who would be eligible for the interventions. These data will be similar to the aggregate DHIS indicators routinely reported to the Department of Health and will not pertain to individual human subjects.

Unit cost data for Objective 7 will be collected from invoices and price lists and from other public sector information sources. These data will not pertain to individual human subjects.

To describe the care cascade and treatment adherence for TB, hypertension and diabetes under Objective 8, routine data collection at clinics will need to be strengthened. We and the NDOH, supported by implementing partners, will assist sites that are not already using it to adopt the “Chronic Patient Record” included in the NDOH’s Integrated Chronic Disease Management (ICDM) Manual (Tool 29 on pages 110-11 of the manual, Appendix III)[14]. (Provincial DOH Chronic Patient Records may also be used) This form, if fully completed, will contain most of the data required to achieve Objective 8. Forms will be linked to other patient records, such as the PHC Tick Register, Adherence Plan and NHLS laboratory test reports, as needed to provide the full data set.

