## **b. Rationale**

Although there is some published or unpublished evidence of the effectiveness of each of these interventions for HIV care[7–9], most have not been implemented jointly or at scale, nor have they been evaluated as delivered routinely by public sector facilities, without external technical assistance or resource support. South Africa also lacks evidence on HIV/NCD co-morbidities and on the prevalence and current treatment outcomes of patients presenting with NCDs. Better information is needed to guide the NDOH’s rollout of the minimum package at national scale and about the number of patients requiring intervention and the cost of delivering the interventions to them.

Prior to national scale-up of the Adherence Guidelines, NDOH intends to select 12 clinics (primary health care clinics and community health centres) for early implementation of the minimum package for HIV patients. This will generate information to refine the guidelines, gain experience in implementation, and project budgetary needs. To maximize the learning potential of these early implementation sites, they will be matched with 12 other clinics and then one clinic in each pair will be randomly assigned to receive the interventions, with the other clinic in the pair serving as a comparison site. This will allow for a cluster-randomized evaluation of the impact of the interventions. The early implementation sites will also generate data on the costs of the interventions and on how to tailor and target the interventions to tuberculosis, hypertension, and diabetes. At the request of the NDOH, we previously developed a set of cost estimates for national implementation of the Adherence Guidelines using published sources of data[16]; this evaluation will also allow refinement of the cost estimates, which are needed to assure sufficient resources for large-scale delivery.

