## **a. Fast Track ART Initiation Counseling**

Fast track initiation seeks to reduce attrition from chronic care by speeding up the process of treatment initiation for patients who are eligible for treatment and thereby increasing the proportion of treatment-eligible patients who start treatment promptly. For HIV, the goal is to reduce the total number of visits that patients need to complete in order to start treatment and allow patients to initiate treatment over the course of two clinic visits within one week of confirming ART eligibility, with additional counseling provided in the first two routine visits after treatment initiation. The intervention includes a detailed curriculum for the counseling sessions, and providers work with patients to create an individualized adherence plan and ensure post-initiation adherence support[12].

| *Primary outcome:* | Proportion of ART-eligible patients who initiate ART (obtain their first supply of ARV medications) within 30 days of determination of treatment eligibility |
| --- | --- |
| *Eligibility:* | All non-pregnant adult patients who are eligible for ART according to national guidelines (CD4 cell count ≤ 500 or Stage 3 or 4 condition) |
| *Sample size:* | 720 (360 per arm; 30 per cluster) |
| *Data sources:* | HIV counseling and testing (HCT) and CD4 count registers; adherence plans; Tier.Net (South Africa’s national HIV patient care database); counselling registers and other registers or records that document services received prior to ART initiation (including patient record) |

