- *Setting*. Both sites in each pair should draw from the same type of community: urban; informal settlement; or rural.
- *Location*. Pairs should be located relatively nearby one another, to facilitate data collection and increase similarity of the catchment populations.

- *HIV viral suppression*. The clinics in the pair should have ART patient viral suppression rates within 10% percent of one another (if data available).

Letters indicating Provincial and District Department of Health authorization to work at each study site have been obtained and are attached. The final number of clinics selected remains at 24 clusters.

In each pair, one clinic will randomly be assigned to receive early implementation of the minimum package of interventions, while the other will continue to provide standard of care. Randomization will be done through a random number generator in Microsoft Excel with a 1:1 ratio of allocation to intervention and control clusters.

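### Read literally, Protocol section 9a has the study team support the Adherence Plan, a Fast Track component, at comparison clinics that are meant to stay on standard of care

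*Protocol*

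**What the plan says.** Three statements in the Protocol bear on this. No statistical analysis plan was available.

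- **Section 9a (Data Sources)** describes preparatory work on records: "Prior to the start of data collection, we will work with each study clinic to ensure" that mandated registers, stationery and records are properly filled in, "including new documentation called for by the Adherence Guidelines, such as the individual patient Adherence Plan". The same paragraph says that "some strengthening of existing data collection procedures will be required at the facilities where the evaluation will take place".
- **Section 4a (Fast Track ART Initiation Counseling)** describes the intervention. Besides the counselling curriculum, "providers work with patients to create an individualized adherence plan and ensure post-initiation adherence support".
- **Section 8a (Selection and Randomization of Study Sites)** says that one clinic in each pair gets the minimum package, "while the other will continue to provide standard of care". It also says "The final number of clinics selected remains at 24 clusters", that is, 12 per arm.

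Adherence plans are also listed as a data source for Objective 1 (section 4a) and Objective 4 (section 4d), in neither case by arm. They are not listed for Objectives 2, 3 or 5 (sections 4b, 4c, 4e).

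**The concern.** The Adherence Plan is both a record and a piece of counselling. According to section 4a, a provider produces it together with the patient. If study staff see to it that comparison clinics complete it, those clinics may begin to do part of what Fast Track consists of, at the evaluators' own prompting. The comparison would then be between Fast Track and standard care plus an adherence plan, not between Fast Track and standard care.

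Any such effect would most likely shrink the difference between arms. The analysis could not remove it afterwards, because every comparison clinic would have been prepared in the same way. A null result for Objective 1 would then be harder to interpret.

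**Working it through.** The point rests on wording, so the sections are compared first. A power calculation follows as illustration only.

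**Does the section 9a commitment reach comparison clinics?**

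1. Nothing in the sentence limits it to intervention clinics.
2. Earlier in section 9a, the phrase for each study clinic is used when the authors expect data procedures to differ between sites. That can only mean all evaluation sites.
3. Section 9b promises one common set of variables for all patients in Cohorts 1-5. The list that follows includes the completed Adherence Plan fields, where data entry is feasible, with no split by arm.
4. For Objective 8, section 9a names the Adherence Plan among the records to which chronic-disease forms will be linked as needed. Objective 8 covers every site: 24 clinics x (100 screened + 100 diagnosed) = 4,800, the figure in Table 4.
5. The introduction to section 4 names what all sites are assumed to follow: the December 2014 HIV guidelines, Primary Care 101 and the National Health Act. The Adherence Guidelines are not named there, and section 9a itself calls the plan new. It is therefore not described as an existing record at comparison clinics.
6. Section 9d adds site visits at least every 10 days and help with completing routine forms, again without distinction by arm.

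The literal reading therefore covers all 24 clinics and conflicts with section 8a.

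**Which objectives are affected?** Only section 4a describes the plan as intervention content. For Objective 4 it is a data source; section 4d describes that intervention as structured counselling sessions. Objectives 2, 3 and 5 do not list it.

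**What could it cost for Objective 1?** Inputs from sections 10a-10b: p0 = 0.60, p1 = 0.75, m = 30 per clinic, c = 12 clinics per arm, coefficient of variation k = 0.1, alpha 0.05 (two-sided assumed). The Hayes-Bennett formula for matched clusters gives

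power = Phi( sqrt[(c - 2)(p1 - p0)^2 / V] - 1.96 ), with V = p0(1 - p0)/m + p1(1 - p1)/m + k^2(p0^2 + p1^2).

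As planned: V = 0.24/30 + 0.1875/30 + 0.01 x (0.36 + 0.5625) = 0.0235. Then sqrt(10 x 0.0225/0.0235) = 3.10, and power is about 87%. For 80% power the formula needs about 22 per clinic, or 26.4 after the 20% increase. The stated 30 is thus somewhat conservative and not exactly reproduced, which does not affect this point.

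Now let the plan alone move comparison clinics by a share f of the 15-point effect, so that p0 = 0.60 + 0.15f. The documents give no value for f; the range is assumed. The last column uses 30/1.2 = 25 per clinic, in case the 20% allowance for ineligible patients is used up.

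| f | Comparison rate | Difference (points) | Power, m = 30 | Power, m = 25 |
|---|---|---|---|---|
| 0 | 60.0% | 15.0 | 87% | 83% |
| 0.1 | 61.5% | 13.5 | 79% | 75% |
| 0.2 | 63.0% | 12.0 | 70% | 65% |
| 0.3 | 64.5% | 10.5 | 58% | 53% |
| 0.5 | 67.5% | 7.5 | 34% | 31% |

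**The case against.** The best counter-argument is that section 9a is about record quality and was never meant to bring the plan into comparison clinics. It has several supports.

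- The sentence concerns mandated records. A plan not mandated at a comparison clinic could be taken to fall outside it.
- When the authors mean that a form should be adopted, they say so, as they do for the Chronic Patient Record in the same section. They do not say it of the Adherence Plan.
- Procedures are to be adapted site by site, and the team disclaims any part in service delivery.
- Sections 4e and 11d use the term study clinics loosely, for the places where the interventions are delivered.

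This lowers certainty about the intention but does not remove the conflict. The sentence expressly includes new Adherence Guidelines documents, and the field list does not separate the arms. The team also need not deliver care itself: getting clinic staff to complete the plan would be enough.

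A second argument carries more weight. The powered outcome is ART initiation within 30 days, and Fast Track pursues it chiefly by reducing visits. A plan form does not shorten that pathway. An f near zero is therefore plausible for this outcome. The nine-month outcome (alive, in care, suppressed) seems more open to influence from adherence planning, but that is a judgement. The plan form (Appendix II) is not shown, and sections 4d and 8a indicate that standard care already includes some adherence support.

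A reader might also set section 9a against section 3b, which notes that most of the interventions have not been "evaluated as delivered routinely by public sector facilities, without external technical assistance or resource support". That phrase describes a gap in existing evidence. It is not a commitment about help with records, so no contradiction follows from it.

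**Conclusion.** The conflict between sections 9a, 4a and 8a is real on a literal reading and should be resolved. What follows from it is a risk: one intervention element may enter the comparison arm, with a likely bias toward no difference, mainly in Objective 1. The size is unknown. The figures in the table depend wholly on the assumed share f and are not estimates. Confidence that section 9a is meant to cover comparison clinics is moderate.

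Three stronger readings are tempting, and the documents do not support them:

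- *The team will install the plan everywhere.* The text speaks only of ensuring that records are completed.
- *The comparison arm is contaminated.* Nothing extends the counselling curriculum, the shortened visit schedule, the clubs, decentralized delivery or tracing to comparison clinics, and the effect of the plan alone is not known.
- *Every cohort is affected.* The plan is intervention content only for Objective 1 and a listed data source only for Objectives 1 and 4.

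**What to change.** Amend section 9a so that support for the Adherence Plan and other new Adherence Guidelines documents applies at intervention clinics only. At comparison clinics, limit record strengthening to records already required under the guidelines named in the introduction to section 4.

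Make the consequential edits:

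- In sections 4a, 4d and 9b, and in the Objective 8 record linkage in section 9a, mark the Adherence Plan as an intervention-clinic source.
- State that all Objective 1-5 outcomes come from sources present in both arms (Tier.Net, NHLS, pharmacy and visit records).
- Use Adherence Plan fields only to describe how the intervention was delivered.

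The cost is a short wording amendment and an instruction for site training. The one loss is that plan fields would not be collected from comparison clinics. The Table 3 outcomes for Objectives 1-5 rest on initiation, medication receipt, viral load, survival and return to or retention in care, and none needs the plan. The change should precede site preparation, because a comparator that has been altered cannot be restored.
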